##### Other Somatic Symptoms

Other somatic symptoms are measured with the CSSI-24 [81-83].

Somatic and psychosocial symptoms are also measured with questions from a well-used Swedish survey, Life and Health – Young People (LH-YP) [91]. The questions are in line with the types of questions used in the Health Behavior in School-aged Children study, a cross-national study coordinated by the World Health Organization’s Regional Office for Europe [28].

##### General Health

Self-rated health is measured with a single question: “How do you rate your general health?” The response options range from 1 to 5 (1=very poor, 2=poor, 3=neither good nor poor, 4=good, and 5=very good) [92]. It has been proven to predict mortality and morbidity [93] and to be a valid and reliable item [93,94].

##### Mental Health and Stress

Depressive symptoms are measured with the Children’s Depression Screener (ChilD-S). The ChilD-S is an 8-question validated screening instrument for depressive symptoms designed for children aged 9 to 12 years [95,96]. The recommended cutoff for depression is ≥13 when the child is investigated in psychiatric or psychosomatic care, according to the Swedish translation of the ChilD-S.

The questionnaires also include 8 questions about stress, anxiety, mood, and happiness. These questions are derived from the LH-YP [91].

Stress was also measured with salivary cortisol. Saliva was collected using oral polymer swabs and tubes (Salimetrics LLC). To measure the morning and evening components of the cortisol circadian rhythm, saliva was sampled as soon as possible after awakening while still in bed in the morning and at least 1 hour after last food intake in the evening on a weekday. Collection times were noted. Saliva cortisol has previously been used as a marker of stress for infants, youth, and adults within the research group (eg, with 11- to 12-year-old girls) [97]. The samples were centrifuged and stored at –20 ⁰C in the university hospital in Örebro and then sent on dry ice to the laboratory at the university hospital in Linköping, where they will be analyzed using a commercial enzyme immunoassay method (Salivary Cortisol Enzyme Immunoassay Kit; Salimetrics LLC) [98]. The results will then be sent back to Örebro University Hospital for evaluation.

##### Sleeping Habits

Questions regarding sleeping habits are derived from the LH-YP [91].

##### School Attendance and Function

School attendance and function are measured with 2 questions created by the research group.

##### Physical Activity

A direct measurement of physical activity was obtained using accelerometers with 3 axles (GT3X; ActiGraph) [99]. The participating girls were instructed to wear the accelerometer for 7 days while they were awake.

##### Enjoyment

The validated Physical Activity Enjoyment Scale (PACES) was customized for dance and yoga in this study. PACES was originally developed to measure enjoyment of physical activity and contains 16 items [100,101].

Enjoyment of the intervention was also evaluated with a graphic rating scale [102], which has been proven to have good consistency and stability [103]. The question was “How do you experience dancing/yoga/relaxation while you perform it?” The rating scale ranges from entirely negative to entirely positive.

##### Experiences

To investigate the girls’ experiences of their participation in the intervention and the legal guardians’ experiences of how the girls were influenced by participating in the intervention, qualitative interviews were conducted a few weeks after the intervention ended. The interviews were face-to-face, with the girl and her legal guardian interviewed separately, and semistructured. They were conducted by the same team each year for internal consistency. The interviews were based on open-ended questions from an interview guide, and participants were encouraged to speak freely about their experiences. Prompts (eg, “Could you tell me more?”) were used to obtain richer material.

##### Quality of Life

Quality of life (QOL) is measured with the Kidscreen-10 index [104], which is an instrument with good psychometric features that assesses children’s and adolescents’ subjective health and well-being. It is used in public health and clinical medicine disciplines in multiple countries. An algorithm for mapping the Kidscreen-10 index onto the Child Health Utility Index 9D (CHU9D) utility scores will be used [105].

QOL is also measured with the EuroQol visual analog scale, which represents health status at the moment of evaluation and ranges from 0 (extremely bad) to 100 (excellent quality of life) [106]. Its validity and reliability are reported to be good [107,108].

##### Resource Usage

Both the girls and their legal guardians are asked about resource consumption, such as visits to primary care, school health care, and other open care. These questions were created by the research group.

##### Food Habits

Questions about food habits were derived from the LH-YP [91].

#### Covariates

To assess covariates, we asked about (1) demographics; (2) parental abdominal and gastrointestinal morbidity; (3) the girl’s background, including mode of delivery (caesarean or vaginal), antibiotic consumption early in life, dance and yoga experiences, menarche, etc; and (4) safety at home, in school, during leisure time activities, on social media, and at other places were the girls spend their time.

### Analyses

#### Statistical Analysis

The Just in TIME study follows the intention-to-treat paradigm. Complementary analyses will be performed per protocol and according to the number of sessions the participant attends.

For baseline statistics between the groups, descriptions will be constructed using frequencies and proportions for categorical data and means and standard deviations for continuous variables. Baseline characteristics will be compared using the Fisher exact test for dichotomous outcomes, the Mantel-Haenszel chi-square test for ordered categorical outcomes, and the Mann-Whitney U test or unpaired *t* test for continuous outcomes. A *P* value of <.05 for the 2-tailed test will be considered statistically significant for all outcomes. When deemed necessary, correction for multiple significance will be performed.

The primary outcome analysis will initially be performed using a Fisher exact test to evaluate differences between groups. To analyze the change in scores from baseline between groups for approximately normally distributed variables, a repeated-measures covariance pattern mixed model will be used, adjusting for significant differences at baseline. To identify predictive factors at baseline that might be associated with the primary outcome, a univariable logistic regression analysis followed by a stepwise multiple logistic regression analysis will be performed.

The distribution of continuous variables will be described using the mean and standard deviation or median and interquartile range. Categorical variables will be described with numbers and percentages.

Study participants who choose to leave the intervention before the study is finished are encouraged to complete all assessments. Missing data will be handled with multiple imputations or within the mixed model.

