#### Inclusion Criteria

Inclusion criteria followed the diagnostic criteria for childhood functional abdominal pain in Rome III [2]: (1) episodic or continuous abdominal pain at least once per week for at least 2 months before diagnosis; (2) insufficient criteria for other FGIDs; and (3) no evidence of an inflammatory, anatomic, metabolic, or neoplastic process that explains the patient’s symptoms.

The following criteria were tested to exclude other illnesses: (1) physical examination including normal growth pattern and (2) laboratory screening, including serological screening with immunoglobulin A antibodies against type 2 (tissue) transglutaminase (TGA-IgA), complete blood cell count, erythrocyte sedimentation rate or C-reactive protein, and urine analysis. A fecal calprotectin test was also included if the girl reported symptoms such as diarrhea.

Diagnostic criteria for IBS in Rome III [2] were used. First, at least once per week for at least 2 months before diagnosis, the patient must have had abdominal discomfort or pain associated with 2 or more of the following at least 25% of the time: (1) improved with defecation, (2) onset associated with a change in the frequency of stool, or (3) onset associated with a change in the form (appearance) of stool. Second, there must be no evidence of an inflammatory, anatomic, metabolic, or neoplastic process that explains the patient’s symptoms.

The following criteria were tested to exclude other illnesses: (1) physical examination including normal growth pattern and (2) laboratory screening including serological screening with TGA-IgA, complete blood cell count, erythrocyte sedimentation rate or C-reactive protein, and urine analysis. A fecal calprotectin test was also included if the girl reported symptoms such as diarrhea.

Persistent pain after examination at the pediatric center was measured with a pain diary at baseline. Girls who reported one or more episodes of pain with a pain score of 4 or higher on the faces pain scale-revised (FPS-r) [76,77] during a full week were eligible for the study.

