#### Randomization

When the baseline measurement was completed and the eligibility check was accomplished, the sample was randomized into an intervention group and a control group. Randomization was performed by an external statistician using minimization based on pain intensity and age at baseline [78].

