#### Sample Size

The total number of required study participants was calculated for the primary outcome (decreased maximal pain after 8 months). The calculation was based on several assumptions. First, we considered the expected proportion of participants who decreased their maximal pain after 8 months in the intervention group. We estimated that 30% of the intervention group would decrease their maximal pain after 8 months based on previous research with CBT, in which approximately 50% of participants were pain free immediately after the intervention [79]. Second, we calculated the expected proportion of participants whose maximal pain would decrease after 8 months in the control group. In previous CBT studies, approximately 25% of control participants reported being pain free when the intervention ended [79]. Since only girls with a long duration of abdominal pain were included in the present study, we estimated that the placebo effect would be smaller and that 10% of the girls in the control group would report decreased maximal pain at the 8-month follow-up. Third, dropout is a common problem that can bias outcomes. A 20% to 50% dropout rate is commonly reported in studies of participants with long-lasting pain [80]. In the present study, a 20% dropout rate was estimated.

With a power of 80% and a significance level of .05, we calculated the sample size to be N=150 (75 intervention + 75 control participants), including a 20% dropout. To decrease bias, a minimum of 50 participants in each group is recommended in trials studying intervention effects on pain, according to previous literature [80].

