#### Primary Outcome Measure

The primary outcome is the proportion of girls in each group who have reduced maximal pain, measured immediately after the intervention (8-month follow-up) with the FPS-r [76,77] in a pain diary in which the girls register their abdominal pain 3 times a day for 1 week. The psychometric features for the FPS-r are reported to be good [77].

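### The unadjusted Fisher exact test named as primary is valid but conservative, ignores the minimisation factors, and does not deliver the stated 80% power

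*Protocol article*

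**What the plan says.** Three statements in the protocol article bear on this.

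- **Allocation** (Randomization): "Randomization was performed by an external statistician using minimization based on pain intensity and age at baseline".
- **Endpoint** (Primary Outcome Measure), defined as follows: "The primary outcome is the proportion of girls in each group who have reduced maximal pain, measured immediately after the intervention (8-month follow-up"). Whether a girl has reduced pain is judged against her own baseline.
- **Primary test** (Statistical Analysis): "The primary outcome analysis will initially be performed using a Fisher exact test to evaluate differences between groups".

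The same section describes two models. The mixed model is for change scores that are roughly normal, and it adjusts only for baseline variables found to differ significantly between the arms. The logistic regression, univariable and then stepwise, is a search for baseline predictors of the primary outcome. Neither is an adjusted comparison of the arms on the binary endpoint. The word *initially* suggests that more will follow, but no such comparison is named.

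The Sample Size section plans on these rates: "We estimated that 30% of the intervention group would decrease their maximal pain after 8 months" and "10% of the girls in the control group would report decreased maximal pain at the 8-month follow-up". It arrives at 150 girls, including 20% dropout, "With a power of 80% and a significance level of .05".

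**The concern.** Two features of the named test cost power.

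First, Fisher's test conditions on both margins of a 2x2 table. Its P value can take few values at these sample sizes, so the true type I error lies well below the nominal level. A sample size from a large-sample formula does not allow for this.

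Second, minimisation makes the arms alike on pain intensity and age. If those factors predict the outcome, an analysis that leaves them out overstates the variance of the arm difference and becomes more conservative still. Baseline pain is a plausible predictor here because the endpoint is a fall from it.

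At stake is the chance of detecting the effect the trial was designed for, in a study that allocated 121 girls against a target of 150.

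**Working it through.** **Inputs.** From Sample Size: 30% versus 10%, 80% power, alpha .05, 20% dropout, 75 per arm. From Statistical Analysis: 2-tailed tests. From Results: 64 and 57 girls allocated.

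**1. Reproducing 150.** The arcsine formula is n per arm = 2[(1.960 + 0.842)/h]², with h = 2·arcsin(√0.30) − 2·arcsin(√0.10) = 0.516. This gives 60 per arm after rounding up. Then 60/0.8 = 75 per arm, or 150 in total, as stated. The pooled normal formula gives 62 per arm; multiplied by 1.2 that is also 75 when rounded up. The continuity-corrected formula, which approximates Fisher's test, gives 72 per arm, then 72/0.8 = 90 per arm, or 180. The stated number therefore fits a large-sample test and not a Fisher-type one.

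**2. Fisher's true size and power.** All possible 2x2 tables were enumerated at a 2-sided nominal 0.05. Size is shown for common responder rates of 10%, 20% and 30%; power is for 30% versus 10%.

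| Evaluable girls | Fisher size | Fisher power | Chi-square power |
|---|---|---|---|
| 60 v 60 (75 less 20%) | 2.2, 2.8, 3.1% | 73.0% | 80.2% |
| 64 v 57 (no dropout) | 3.4, 3.9, 3.9% | 77.3% | 81.2% |
| 51 v 46 (64 and 57, less 20%) | 3.0, 3.6, 3.8% | 66.3% | 71.0% |

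The chi-square test is uncorrected, and its size in these settings is 4.7 to 5.4%. With 20% dropout, the loss from discreteness is 80.2 − 73.0 = 7.2 points at the planned size and 71.0 − 66.3 = 4.7 points at the allocated size.

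Fisher's test first reaches 80% power at 69 evaluable per arm. Then 69/0.8 = 86.25, so 87 per arm, or 174 in total.

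**3. Leaving out the minimisation factors.** This was simulated at marginal rates of 30% and 10%, with biased-coin minimisation on four pain levels and two age groups and 4,000 trials per setting. The article gives no prognostic strength, so the log-odds slope per pain level was varied from 0 to 1.2, with half that value for age group. The adjusted test here is the likelihood-ratio test from a logistic model with arm, pain and age.

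| Completers | Slope | Fisher power | Chi-square power | Adjusted power |
|---|---|---|---|---|
| 120 | 0 | 75.1% | 80.7% | 81.5% |
| 120 | 0.4 | 75.3% | 81.1% | 82.9% |
| 120 | 0.8 | 76.3% | 82.1% | 85.8% |
| 120 | 1.2 | 78.1% | 83.8% | 90.2% |
| 97 | 0 | 68.0% | 72.1% | 73.8% |
| 97 | 0.4 | 67.9% | 72.7% | 75.3% |
| 97 | 0.8 | 67.2% | 72.4% | 77.8% |
| 97 | 1.2 | 67.7% | 73.3% | 82.6% |

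Under the null at 120 completers, Fisher's rejection rate falls from 2.6% at slope 0 to 1.6% at slope 1.2, and the chi-square's from 4.7% to 3.3%. This is the added conservatism from ignoring balanced prognostic factors.

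The likelihood-ratio test is slightly liberal, rejecting 5.6 to 6.7% under the null over both sizes, so its gain is a little overstated. A score test of the same model, simulated separately, had size of about 5 to 6% and power of 72 to 82% at 97 completers and 81 to 89% at 120. Against the chi-square, that puts the gain from adjustment itself at about 0 to 8 points.

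**The case against.** The best defence is that Fisher's test is valid. It does not inflate the type I error, and its conservatism works against a false claim of benefit. It is also a natural choice with few events: at 51 versus 46 and the planned rates, 51 × 0.30 + 46 × 0.10 ≈ 15 + 5 = 20 responders are expected. For a model with three coefficients besides the intercept, that is about 6 to 7 events each, which is sparse. All of this stands. It rules out calling the test wrong, and it limits how large the adjusted model may be.

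Three stronger readings are tempting but not supported.

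- **That the ignored minimisation factors explain the loss.** If pain and age are weakly prognostic, nearly all of it is Fisher's discreteness, and an unadjusted chi-square would recover it. The article gives no prognostic strength. It also does not say that the pain intensity used for minimisation is the maximal FPS-r score.
- **That the primary analysis has no workable route for missing data.** A Fisher P value does not fit Rubin's rules, and the mixed model does not cover a binary endpoint. But the article says "Missing data will be handled with multiple imputations or within the mixed model", and a risk difference or log odds ratio from the same 2x2 table can be pooled over imputations. How imputation joins the test is detail that an article may leave to an analysis plan. Nothing in the text says that the result will rest on complete cases.
- **That the gain is much larger.** Simulations with responder rates of around 40% and 66% can show bigger gaps, but the protocol plans on 10% and 30%.

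**Conclusion.** The point holds as one of efficiency. The primary test is valid but conservative, and it does not deliver the 80% power stated for 150 girls: at the protocol's own rates and dropout it delivers 73%. At the 121 allocated less 20% dropout it delivers about 66%. About 5 to 7 points of the shortfall against a chi-square test follow from enumeration alone, given 30% versus 10% and 20% dropout. The further 0 to 8 points from adjusting for pain and age rest on an assumed slope of 0 to 1.2 in the log odds per pain level, and could be near zero. There is no threat of false positives, and the shortfall in recruitment is a separate cause of lost power.

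**What to change.** Prespecify one adjusted comparison as primary, before the 8-month outcome is compared by arm. If that comparison has already been made, report the adjusted result as post hoc.

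- Fit a logistic regression of reduced maximal pain on arm, with baseline pain and age as the only covariates. State which pain measure the minimisation used, and enter baseline pain as the maximal FPS-r score.
- Test the arm effect with a score test, or report a standardised risk difference with 95% CI. Avoid the likelihood-ratio test, which was slightly liberal.
- Pool that estimate over the multiple imputations already planned.
- Keep Fisher's test as the unadjusted supportive analysis, and keep the stepwise regression apart as a predictor search.
- State the power of the chosen test at the number actually allocated.

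The cost is a few sentences. Pain and age were needed for allocation, so they exist for every randomised girl. The drawback is sparseness with about 20 expected responders, which is why no further covariates should be added.

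### The mixed models for secondary scores choose covariates by significant baseline differences, a rule that picks chance imbalances and will practically never pick the minimised factors, pain intensity and age

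*Protocol article*

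**What the plan says.** All quotations are from the protocol article.

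- **Allocation (Randomization):** "Randomization was performed by an external statistician using minimization based on pain intensity and age at baseline".
- **Baseline tests (Statistical Analysis):** "Baseline characteristics will be compared using the Fisher exact test for dichotomous outcomes", with corresponding tests for ordered and continuous variables. A P value below .05 "for the 2-tailed test will be considered statistically significant for all outcomes".
- **Model for scores (Statistical Analysis):** "To analyze the change in scores from baseline between groups for approximately normally distributed variables", the plan is that "a repeated-measures covariance pattern mixed model will be used, adjusting for significant differences at baseline". No other covariate is named for this model, and the article nowhere says that the minimisation factors enter a treatment comparison.
- **Candidate variables (Covariates):** "To assess covariates, we asked about (1) demographics; (2) parental abdominal and gastrointestinal morbidity", followed by the girl's background and her safety in various settings. The list is open-ended and gives no count.
- **Primary outcome (Statistical Analysis):** "The primary outcome analysis will initially be performed using a Fisher exact test to evaluate differences between groups". It has no covariates.

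**The concern.** A covariate earns its place in a randomised comparison by predicting the outcome. A significant baseline difference between randomised arms is a chance event and carries no information about prediction. The rule therefore admits variables for the wrong reason, and the covariate set is unknown until the arms have been compared at baseline.

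Minimisation adds a second problem. It forces the arms to agree on pain intensity and age, so a test for a difference on either will almost never be significant. Yet these are the factors that an analysis should carry after minimisation, because the standard error otherwise ignores the balance that was built in.

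At stake are precision and power for the secondary scores analysed by this model and, for outcomes closely tied to a minimised factor, a test that runs below its nominal level.

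**Working it through.** The plan gives no figure for this rule. Its sample-size calculation concerns the primary outcome and does not enter here.

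**1. How often would the rule select a minimised factor?**
Minimisation on pain and age was simulated for 121 girls (the number allocated, Results) and for 150 (the target, Sample Size), followed by the planned baseline tests at two-sided .05, with 3000 trials per setting. The article gives neither category cut-points nor an assignment probability. Fine and two-level categories, and deterministic and 0.8 biased-coin assignment, were therefore tried, with an assumed pain distribution.

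| Allocation | Pain significant | Age significant |
|---|---|---|
| Simple randomisation | 4.4-4.6% | 4.9-5.0% |
| Minimisation, all settings | 0% | 0-0.1% |

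**2. What does it select instead?**
Each variable that was not minimised has a 5% chance of a significant difference. For k independent variables the chance of at least one is 1 - 0.95^k, and the expected number is 0.05k. The article does not give k, so a range is shown.

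| k | At least one | Expected number |
|---|---|---|
| 5 | 23% | 0.25 |
| 10 | 40% | 0.5 |
| 20 | 64% | 1.0 |
| 30 | 79% | 1.5 |

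**3. Power if the outcome's own baseline is not in the model**
Assumptions, none given in the article: one follow-up time, equal variances (SD 1), an effect of 0.5 SD, and a baseline-to-follow-up correlation r of 0.4 or 0.6. For the number analysed, 121 x 0.8 = 96.8, taken as 49 per arm (98).

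- Change score: variance 2(1 - r), SE = sqrt(2 x 2(1 - r)/49).
- Baseline-adjusted: residual variance 1 - r², SE = sqrt(2 x (1 - r²)/49).
- Power is approximately Φ(0.5/SE - 1.96).

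| r | Variance, change v adjusted | SE | Power by formula | Power, simulated range |
|---|---|---|---|---|
| 0.4 | 1.20 v 0.84 | 0.221 v 0.185 | 62% v 77% | 60-65% v 74-78% |
| 0.6 | 0.80 v 0.64 | 0.181 v 0.162 | 79% v 87% | 78-81% v 86-87% |

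The simulated ranges cover allocation balanced and not balanced on the baseline score. The gap appears in both, so it comes from omitting the baseline covariate and not from minimisation.

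**4. Level of the unadjusted test**
If allocation is balanced on the outcome's own baseline, the change-score contrast varies only with variance 1 - r², while the test uses 2(1 - r). The true level is 2Φ(-1.96 x sqrt[2(1 - r)/(1 - r²)]).

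- r = 0.4: 1.96 x sqrt(1.20/0.84) = 2.34, level 1.9%.
- r = 0.6: 1.96 x sqrt(0.80/0.64) = 2.19, level 2.8%.
- Simulation under this balance gave about 2% (2.1-2.4%), with the baseline score never selected.

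Without that balance the effect disappears. In simulation at r = 0.4, balancing only on a factor correlated 0.3 with the outcome's baseline gave a level of 4.9%, with that baseline selected in 3.9% of trials. With no balancing the figures were 5.4% and 5.1%.

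**The case against.** Four arguments favour the plan.

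- **The rule cannot touch the main conclusion.** It covers only approximately normal scores, and the primary outcome is a proportion tested by Fisher's exact test. This stands and limits the severity.
- **The model may already use the outcome's baseline.** The article does not say whether baseline is a response in the repeated vector, a covariate or merely subtracted, and a condensed article need not say so. This stands in part, which is why the power loss is stated conditionally. Subtraction alone would not remove it, because that fixes the baseline slope at 1 and does nothing for age.
- **Selection uses baseline data under a stated threshold.** It cannot be steered by the treatment effect. This stands: the fault is that the rule ignores prognostic value, not that it invites outcome-driven choice. The article also allows for multiplicity correction where needed; applied to the baseline tests, it would reduce the number of chance covariates.
- **The sizes rest on assumed inputs.** They do, and they are labelled and given as ranges.

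A reader might infer that the test level is wrong for every secondary outcome. The article does not support that. Depression, quality of life, self-rated health, cortisol and accelerometry were not minimisation factors, and the level moves materially only where the outcome is strongly correlated with a minimised factor. A reader might also infer extra false positives; where the level moves in these calculations, it moves down.

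**Conclusion.** The concern holds for the repeated-measures models of approximately normal secondary scores. The article states a covariate rule outright, so this is not detail left to an analysis plan, and the rule performs worse than a fixed set. That it passes over pain intensity and age is practically certain but not an explicit exclusion: selection was 0% for pain and at most 0.1% for age under the assumed minimisation settings.

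If the outcome's own baseline is also absent, the cost is about 15 percentage points of power at a correlation of 0.4 (62% v 77%) and about 8 at 0.6 (79% v 87%), for 98 girls and a 0.5 SD effect. The conservative level of about 2% applies chiefly to pain scores; elsewhere it stays near 5%. The severity is below must-fix because the primary analysis and the sample size are unaffected.

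**What to change.** In the Statistical Analysis section, delete the clause after the comma in "a repeated-measures covariance pattern mixed model will be used, adjusting for significant differences at baseline". State instead that every such model adjusts for:

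- the baseline value of the outcome;
- baseline pain intensity, as used in the minimisation;
- age.

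These enter whatever the baseline P values. Where the outcome is itself the pain measure used in the minimisation, its baseline enters once. City and intake wave may be added, but they are not stated as minimisation factors and the argument does not require them. Baseline tests may still be reported if wanted, but they should not determine the model.

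The cost is about one sentence. The variables are already collected and the planned sample size does not change. The amendment should be dated and documented before outcomes are compared by arm.

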#### Secondary Outcome Measures

##### Abdominal Pain and Gastrointestinal Issues

Abdominal pain is measured with the pain diaries with the FPS-r [76,77].

Abdominal pain is also measured in the questionnaires with a subscale in the Children’s Somatic Symptoms Inventory-24 (CSSI-24) (formerly known as the Children’s Somatization Inventory) [81-84]. The CSSI-24 is a valid and reliable instrument that assesses a variety of nonspecific somatic symptoms [81].

Pain drawings are used to elicit information about the location of pain symptoms [85,86]. A growing body of evidence supports pain drawings as an assessment of pain among children [85].

Fecal samples were collected at baseline and at 8 months for measurement of the intestinal bacterial composition. This is an important background variable that can affect how effective the intervention is for a participant and thus has prognostic significance for the treatment outcome [87].

The Bristol stool chart (BSC) is a well-recognized tool designed to classify the form and consistency of feces into 7 categories [88]. It is used in both clinical and experimental fields [89] and has been used to assess the intestinal transit rate. Normal stool consistency is considered type 3 to type 5 on the BSC [90].

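### Baseline predictors are to be chosen by univariable and then stepwise logistic regression on about 20 to 25 expected events, too few for stable selection

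*Protocol article*

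**What the plan says.** The Statistical Analysis section gives the purpose, "To identify predictive factors at baseline that might be associated with the primary outcome", and fixes the method: "a univariable logistic regression analysis followed by a stepwise multiple logistic regression analysis will be performed". The outcome is binary: "The primary outcome is the proportion of girls in each group who have reduced maximal pain", assessed at 8 months.

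The Sample Size section supplies the expected rates: "We estimated that 30% of the intervention group would decrease their maximal pain after 8 months", and "10% of the girls in the control group would report decreased maximal pain at the 8-month follow-up". It adds: "In the present study, a 20% dropout rate was estimated". The Results section reports 64 girls allocated to the intervention and 57 to control, against a planned 75 and 75.

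The Covariates section lists background items that were asked about: demographics, parental gastrointestinal morbidity, a set that includes "mode of delivery (caesarean or vaginal), antibiotic consumption early in life, dance and yoga experiences, menarche", and feelings of safety in several settings. The list is open-ended, and the section does not say which items enter the regression. A two-tailed P<.05 applies to all outcomes, with multiplicity correction left to judgement.

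**The concern.** Univariable testing followed by stepwise selection uses the same small data set to choose predictors and to estimate their effects. With few events per candidate this has three known results:

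- The set of factors selected changes with small changes in the data.
- The factors that survive do so partly because their estimates came out large by chance, so their odds ratios are overstated.
- The reported P values and intervals are computed as if the final model had been chosen in advance.

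At stake is the credibility of any statement about which baseline features go with improvement. A chance association could be published as a predictor and carried into later studies or practice. The objection is to a method that the article states, not to detail that it omits.

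**Working it through.** **Inputs.** Responder rates 30% and 10%, dropout 20%, power 80%, alpha .05 (Sample Size); 64 and 57 allocated (Results); two-tailed tests (Statistical Analysis). The number of candidates is an assumption, 10 to 20.

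**The plan's own figure.** For 30% against 10%, the pooled normal-approximation formula is n = [1.96 × √(2 × 0.20 × 0.80) + 0.84 × √(0.21 + 0.09)]² / 0.20², which gives 62 per arm. Then 62 × 1.2 = 74.4, rounded up to 75 per arm, or 150 in total. The stated N is reproduced with dropout added as a factor of 1.2, so these rates are the ones the plan was built on.

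**Expected events (responders).**

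| Scenario | Intervention | Control | Total | After 20% loss |
|---|---|---|---|---|
| Planned 75 + 75, 30%/10% | 22.5 | 7.5 | 30.0 | 24.0 |
| Allocated 64 + 57, 30%/10% | 19.2 | 5.7 | 24.9 | 19.9 |
| Allocated 64 + 57, 50%/25% | 32.0 | 14.25 | 46.25 | 37.0 |

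The last row uses the pain-free rates that the Sample Size section cites from earlier cognitive behavioural therapy (CBT) research.

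**Number of candidates.** Counting the Covariates section item by item gives roughly 11: demographics (at least 1), parental morbidity (1), delivery mode, early antibiotics, dance and yoga experience and menarche (4), and safety in five settings (5). This count is a reading of the list. Baseline symptom scales and biomarkers could be added, and a shorter list could be used.

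**Events per candidate at the planning rates.**
- 10 candidates: 19.9/10 = 2.0 to 24.9/10 = 2.5
- 15 candidates: 19.9/15 = 1.3 to 24.9/15 = 1.7
- 20 candidates: 19.9/20 = 1.0 to 24.9/20 = 1.2

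At the cited CBT rates the range is 37/20 = 1.9 to 46.25/10 = 4.6. The limiting number in logistic regression is the smaller of events and non-events. It cannot exceed 60 of 121, so no responder rate gives more than 60/10 = 6.0 per candidate with 10 candidates, or 60/20 = 3.0 with 20.

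**False univariable findings.** If all k candidates are null and independent, the chance of at least one P<.05 is 1 − 0.95^k: 40% for k = 10 and 64% for k = 20.

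**Simulation of the whole procedure.** Pure-noise candidates, half of them binary, were screened at P<.20 and then reduced by backward elimination at P<.05. Both thresholds are assumptions. There were 600 runs per setting, at 64/57 and at 51/46 (after dropout).

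| Candidates | Trials keeping at least one false predictor | Mean apparent AUC when any was kept |
|---|---|---|
| 10 | 35% to 40% | 0.66 to 0.68 |
| 15 | 51% to 54% | 0.67 to 0.69 |
| 20 | 63% | 0.68 to 0.71 |

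The true AUC is 0.50 throughout.

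**The case against.** Several points on the other side are fair.

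- **The event count is an expectation.** The planning rates were set below the cited CBT rates. At those higher rates there would be 37 to 46 events. This stands as a range, but even then there are fewer than 5 events per candidate.
- **The candidate list is not in the document.** The Covariates items are not tied to the regression, and an analysis plan not shown may name a short list. This stands. The events per candidate and the 40% and 64% figures depend on the assumed 10 to 20, and correlated items, such as safety in different settings, would lower those percentages.
- **The analysis is secondary and tentatively worded.** This also stands, and it limits the weight of the point.

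A reader might go further and infer that the stated model fails to show which girls benefit from dance and yoga, because it has no arm-by-factor term. Support might be sought in the section on abdominal pain and gastrointestinal issues, which says of the gut microbiota: "This is an important background variable that can affect how effective the intervention is for a participant and thus has prognostic significance". The documents do not carry that reading. That sentence explains why fecal samples are taken and is not linked to the regression. The stated aim of the regression is only association with the outcome. The lack of an interaction term is inferred from silence in a condensed article. A reader might also infer that the reported predictors would be mostly noise. The simulation does not show this: with 10 candidates, all of them null, most trials kept none.

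**Conclusion.** The concern holds as a minor point about a stated method. With about 20 to 25 expected events at the plan's own rates, and about 1 to 2.5 per candidate if 10 to 20 candidates are examined, univariable testing followed by stepwise selection is unstable, overstates the odds ratios of the factors kept, and yields P values that ignore the selection. Under an all-null, independent set, a false univariable finding has a 40% to 64% chance. These sizes rest on the planning rates, the numbers allocated and an assumed candidate count, but the direction does not change at the cited CBT rates. The Fisher exact test of the primary outcome is untouched. Whatever is found should be described as prognostic association with pain reduction and not as evidence of who gains from the intervention.

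**What to change.** Replace the univariable and stepwise steps with one penalised logistic model, for example ridge or lasso. Include arm, baseline maximal pain, age (pain intensity and age being the minimisation factors) and a short list of candidates named before the outcome data are examined. Report performance corrected for optimism by bootstrap, repeating the whole fitting process in each resample. Label the analysis exploratory and its results prognostic.

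Interaction tests are not recommended as the main remedy: only about 5 control-arm events are expected (57 × 0.10 = 5.7, or 4.6 after dropout), so any such estimate would be very imprecise.

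The cost is a change of analysis wording and the use of standard software. The downside is that fewer candidate factors can be examined. Penalisation does not create information: with this few events the list has to be short and the estimates will still be imprecise.
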